#### Exploratory endpoints

Response rate according to expression of PD-L1. PD-L1 expression will be determined by immunohistochemistry in QualTek Molecular Laboratories on an archival or newly obtained tissue sample of the tumor or metastatic lesion.Immunologic response in peripheral blood samples analyzed via fluorescence-activated cell sorting (FACS) phenotyping, ultra-performance liquid chromatography (UPLC) and enzyme-linked immunesorbent assay (ELISA).

### Study population

#### Inclusion criteria

Be willing and able to provide written informed consent/assent for the trial.Be ≥18 years of age on day of signing informed consent.Have at least two measurable lesions according to RECIST v1.1.Have had any prior treatment more than 2 weeks prior to study day 1, treatment naïve patients are allowed.Histological confirmed diagnosis of urothelial carcinoma.Be willing to provide tissue from a newly obtained core or excisional biopsy of a tumor lesion. *Newly*-*obtained is defined as a specimen obtained up to 6* *weeks (42* *days) prior to initiation of treatment on day 1. Subjects for whom newly*-*obtained samples cannot be provided (e.g. inaccessible or subject safety concern) may submit an archived specimen only upon agreement from the sponsor.*
Have a performance status of 0 or 1 on the ECOG performance scale.Demonstrate adequate organ function as defined in Table 1, all screening labs should be performed within 10 days before treatment initiation.

**Table 1 Tab1:** Adequate organ function laboratory values

System	Laboratory value
Hematological	
Absolute neutrophil count	≥1500/mcL
Platelets	≥100,000/mcL
Hemoglobin	≥9 g/dL or ≥5.6 mmol/L without transfusion or EPO dependency (within 7 days of assessment)
Renal	
Serum creatinine *OR* Measured or calculated^a^ creatinine clearance	≤1.5 X upper limit of normal (ULN) *OR* ≥60 mL/min for subject with creatinine levels >1.5 X institutional ULN
Hepatic	
Serum total bilirubin	≤1.5 X ULN *OR*
	Direct bilirubin ≤ULN for subjects with total bilirubin levels >1.5 ULN
AST (SGOT) and ALT (SGPT)	≤2.5 X ULN *OR* ≤5 X ULN for subjects with liver metastases
Albumin	≥25 g/L
Coagulation	
International normalized ratio (INR) or prothrombin time (PT) Activated partial thromboplastin time (aPTT)	≤1.5 X ULN unless subject is receiving anticoagulant therapy as long as PT or PTT is within therapeutic range of intended use of anticoagulants ≤1.5 X ULN unless subject is receiving anticoagulant therapy as long as PT or PTT is within therapeutic range of intended use of anticoagulants

^a^Creatinine clearance should be calculated per institutional standardFemale subjects of childbearing potential should have a negative urine or serum pregnancy within 72 h prior to receiving the first dose of study medication. If the urine test is positive or cannot be confirmed as negative, a serum pregnancy test will be required.Female subjects of childbearing potential must be willing to use an adequate method of contraception for the course of the study through 120 days after the last dose of study medication. *Note: Abstinence is acceptable if this is the usual lifestyle and preferred contraception for the subject.*
Male subjects of childbearing potential must agree to use an adequate method of contraception starting with the first dose of study therapy through 120 days after the last dose of study therapy. *Note: Abstinence is acceptable if this is the usual lifestyle and preferred contraception for the subject.*
The subject is currently not participating or receiving study therapy and has not participated in a study of an investigational agent and received study therapy or used an investigational device within 4 weeks of the first dose of treatment.No prior radiotherapy interfering with SBRT.No diagnosis of immunodeficiency and no systemic steroid therapy or any other form of immunosuppressive therapy within 7 days prior to the first dose of trial treatment.No history of active tuberculosis.No hypersensitivity to pembrolizumab or any of its excipients.Has not received any prior anti-cancer monoclonal antibody within 4 weeks prior to study day 1 or has not recovered (i.e. ≥grade 1 or at baseline) from adverse events due to agents administered more than 4 weeks earlier.No prior chemotherapy, targeted small molecule therapy, or radiation therapy within 2 weeks prior to study day 1 or no recovering (i.e. ≤grade 1 or at baseline) from adverse events due to a previously administered agent.Note: Subjects with ≤grade 2 neuropathy are an exception to this criterion and may qualify for the study.Note: If subject received major surgery, they must have recovered adequately from the toxicity and/or complications from the intervention prior to starting therapy.
No additional malignancy that is progressing or requires active treatment. Exceptions include basal cell carcinoma of the skin or squamous cell carcinoma of the skin that has undergone potentially curative therapy or in situ cervical cancer.No active central nervous system metastases and/or carcinomatous meningitis. Subjects with previously treated brain metastases may participate provided they are stable (without evidence of progression by imaging for at least 4 weeks prior to the first dose of trial treatment and any neurologic symptoms have returned to baseline), have no evidence of new or enlarging brain metastases, and are not using steroids for at least 7 days prior to trial treatment. This exception does not include carcinomatous meningitis which is excluded regardless of clinical stability.No active autoimmune disease that has required systemic treatment in the past 2 years (i.e. with use of disease modifying agents, corticosteroids or immunosuppressive drugs). Replacement therapy (e.g. thyroxine, insulin, or physiologic corticosteroid replacement therapy for adrenal or pituitary insufficiency, etc.) is not considered a form of systemic treatment.No known history of, or any evidence of active, non-infectious pneumonitis.No active infection requiring systemic therapy.No history or current evidence of any condition, therapy, or laboratory abnormality that might confound the results of the trial, interfere with the subject’s participation for the full duration of the trial, or is not in the best interest of the subject to participate, in the opinion of the treating investigator.No known psychiatric or substance abuse disorders that would interfere with cooperation with the requirements of the trial.Is not pregnant or breastfeeding, or expecting to conceive or father children within the projected duration of the trial, starting with the pre-screening or screening visit through 120 days after the last dose of trial treatment.Has not received prior therapy with an anti-PD-1, anti-PD-L1, or anti-PD-L2 agent.No known history of human immunodeficiency virus.No known active hepatitis B or hepatitis C.Subjects should not have received a live vaccine within 30 days of planned start of study therapy.

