### Outcome measures

#### Primary endpoint

DLT occurring between the start of SBRT and 12 weeks after completion of SBRT. DLT will be assessed using the Common Terminology Criteria for Adverse Events (CTCAE) version 4.0. DLT should be, completely or in part, related to trial therapy. The following events will be considered as DLT: any grade 3–5 metabolic or hematological toxicity that is related, probably related or possibly related to pembrolizumab or SBRT.any grade 3–5 non-hematological toxicity that is related, probably related or possibly related to SBRT.

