### Sample size

In the first phase of the trial 20 patients will be recruited and randomly assigned to a treatment arm. If the chance that the posterior toxicity probability rate exceeds 0.2 is more than 0.7 in a certain arm, this arm will be closed.

The secondary endpoint is the assessment of the response rate of the combination treatment in non-irradiated metastases in every arm. For this analysis a Simon’s two-stage optimum design will be used [29]. The arm with the best response rate and with acceptable toxicity will be used to proceed into the second phase. The null hypothesis that the true response rate is 0.21 [10] will be tested against a one-sided alternative. If there are two or fewer responses, the alternative hypothesis will be rejected. Otherwise 13 additional patients will be accrued for a phase II trial. The null hypothesis will be rejected if 7 or more responses are observed in 23 patients. This design yields a type I error rate of 0.15 and power of 0.8 when the true response rate is 0.41 (Table 2). We consider the chance that both arms in phase 1 are deemed safe with equal toxicity and equal response rates very small. Since both arms will then qualify to continue to phase 2, selection of one arm will depend on secondary outcomes available at that time (e.g. PFS, OS).

**Table 2 Tab2:** Simon’s two-stage optimum design

Optimal two stage design	Optimum design
First stage sample size (n1)	10
r1	2
Maximum sample size (n)	23
r2	6

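### Two neighbouring entry criteria on recovery from earlier toxicity are worded in the negative and carry opposite grade signs, so as written they do not require recovery and need reconciling

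*Protocol article*

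**What the plan says.** The list stands under the heading "Inclusion criteria", so each item is a statement that must be true for a patient to enter. Two adjacent items deal with recovery from earlier treatment.

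- **Monoclonal-antibody criterion.** It opens "Has not received any prior anti-cancer monoclonal antibody within 4 weeks prior to study day 1" and continues "or has not recovered (i.e. ≥grade 1 or at baseline) from adverse events due to agents administered more than 4 weeks earlier".
- **Chemotherapy, small-molecule and radiation criterion.** It opens with a two-week washout introduced by a leading *No*, and continues "or no recovering (i.e. ≤grade 1 or at baseline) from adverse events due to a previously administered agent".

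Two notes follow the second item. One exempts patients with neuropathy up to grade 2 and says they may still qualify. The other requires adequate recovery from major surgery before therapy starts.

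Other entry rules bear on the same patients. Table 1 sets haematological, renal, hepatic and coagulation limits, with screening laboratory tests within 10 days of starting treatment. A later item rules out any condition, therapy or laboratory abnormality that the treating investigator thinks might confound the results.

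**The concern.** Most of the list consists of conditions phrased as absences, as if an exclusion list had been turned round. In these two items only the first half appears to have been turned. The recovery half of the antibody item still describes the patient who should be kept out, yet it is joined by *or* to a condition for getting in. The grade sign in its bracket is also the reverse of its neighbour's.

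This is operative text that a screener applies, not background. The same section allows patients whose earlier treatment ended just over two weeks before day 1, so residual toxicity at screening is a realistic situation. The section Study approval and recruitment reports that enrolment had begun. Two things are at stake: the safety of patients who enter with unresolved toxicity, and whether two screeners, or a screener and a monitor, would reach the same decision on the same patient.

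**Working it through.** No arithmetic in the plan rests on this wording, so the check is textual and logical.

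**Step 1: the antibody criterion read literally.** Let A mean no antibody in the last 4 weeks, R mean recovered from earlier agents, and U mean not recovered. As written the item is *A or U*. The evident intention is *A and R*. For now, the bracket is set aside.

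| Patient | As written (*A or U*) | Evident intention (*A and R*) |
|---|---|---|
| No recent antibody, recovered | meets | meets |
| No recent antibody, not recovered | meets | fails |
| Recent antibody, recovered | fails | fails |
| Recent antibody, not recovered | meets | fails |

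The two readings differ in both rows for unrecovered patients. The literal rule turns away only the recent-antibody patient who has recovered.

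**Step 2: the bracket inside the antibody criterion.** It has two parts, ≥grade 1 and at baseline, and there are two ways to attach it.
- If it explains *not recovered*, then ≥grade 1 fits but at baseline does not.
- If it explains *recovered*, then at baseline fits but ≥grade 1 does not, because it takes in every higher grade as well.

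The bracket is inconsistent on either attachment.

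**Step 3: comparison with the neighbour.** There the bracket reads ≤grade 1 or at baseline, which is coherent only as a description of a recovered patient. If the antibody bracket is taken to describe non-recovery, a patient with residual grade 1 toxicity is unrecovered under one criterion and recovered under the next. If it is taken to describe recovery, the inequality points the wrong way. Either way the two items need reconciling.

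**Step 4: can the neighbour simply be used to correct the first item?** Only in part. Its bracket is coherent, but its recovery clause is negated too. If the leading *No* governs both halves, it means no recent therapy and no failure to recover, which is a sensible rule. If the second half is read on its own after *or*, non-recovery again satisfies the criterion. The text does not settle which is meant.

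**Step 5: evidence of intention.** An exception that lets patients with neuropathy up to grade 2 qualify has a purpose only if such toxicity would otherwise bar entry. The surgery note states a recovery requirement directly. Both point to recovery being required.

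**The case against.** The strongest reply is that no reasonable screener would admit a patient because the patient had *not* recovered. The two notes show what is meant. With its leading *No* applied to both halves, the neighbouring criterion requires recovery from any previously administered agent, with no limit on class or time. On that reading the slip in the antibody item admits nobody new. Table 1 and the confounding criterion add further protection.

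Much of this stands. It makes the intention clear and the practical harm limited, but it does not make the rule correct. The neighbour closes the gap only on one of two readings, Table 1 covers laboratory values alone, and the confounding item rests on investigator opinion. None of these replaces a recovery criterion that can be audited.

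Two stronger readings are tempting, and the document does not support either.

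- **A reader might infer that the two criteria cannot both be applied.** They can. Each is an *or* statement, and a patient with no antibody in 4 weeks and no chemotherapy, small molecule or radiation in 2 weeks meets the first half of both. The fault is that the recovery halves do no useful work when read literally, not that they exclude each other.
- **A reader might infer that carried-over toxicity will inflate the primary endpoint and close an arm.** The route exists. The Primary endpoint section accepts partial attribution ("DLT should be, completely or in part, related to trial therapy"), and for metabolic and haematological events a possible relation to either treatment is enough ("any grade 3–5 metabolic or hematological toxicity that is related, probably related or possibly related to pembrolizumab or SBRT"). But the event must also be grade 3–5 and fall between the start of SBRT and 12 weeks after its completion. The remaining category counts only through SBRT ("any grade 3–5 non-hematological toxicity that is related, probably related or possibly related to SBRT"). Nothing in the article indicates how often an old toxicity would meet all these conditions. The closure rule ("If the chance that the posterior toxicity probability rate exceeds 0.2 is more than 0.7 in a certain arm, this arm will be closed") is sensitive to single events in small arms, but that is true of any extra DLT and does not measure this defect. The article also gives no TITE-CRM model or prior from which to compute an effect.

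**Conclusion.** The point holds as a minor correction to an operative eligibility rule. The antibody criterion is wrong as written: its recovery clause is left in exclusion form, its bracket contradicts itself, and its sign is opposite to that of the next criterion, which is also awkwardly negated. Read literally, non-recovery satisfies an entry condition.

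The consequence is mainly for patient safety and uniform screening. No sample size, error rate or other stated figure depends on it, and an effect on the DLT count is conceivable but of unknown size. The conclusion rests on taking the list as conditions that must be true for entry, which its heading supports, and on the article's wording being what is applied at screening. If the full protocol words the two items correctly, only the article needs correcting.

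**What to change.** Reconcile the two criteria. Write each as a washout condition *and* a positive statement that the patient has recovered from adverse events of earlier agents, replacing the present *or* followed by a negative. Make the brackets and the direction of the inequality consistent across the two items, and keep the neuropathy exception attached where it is meant to apply. The level that counts as recovered is for the sponsor to settle.

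The cost is a wording correction at the next amendment. Sample size, randomisation and analysis are unchanged. Since recruitment has started, it would be prudent at the same time to confirm which reading has been used for patients already screened.

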### Intervention

#### SBRT

A total dose of 24 Gy will be delivered to one lesion in 3 fractions with image-guided treatment verification and fractions will be separated >48 and <96 h.

All patients will receive a CT in supine position with 3 mm CT slice thickness through the tumor site. The planning simulation should cover the target and all organs at risk. A typical scan length should extend at least 10 cm superior and inferior beyond the treatment field borders. Support devices to increase patient comfort will be chosen depending on the tumor localization. Lung and liver tumor sites will be simulated with 4D-CT, taking into account breathing. The isocenter will be determined on the CT-simulator with marking of laser lines on the patient. Imaging data will be transferred to the treatment planning system. For all lesions, the gross target volume (GTV) will be defined as all visible tumor by combining iconographic and metabolic information. No additional margin will be added for microscopic spread of disease. The GTV will be expanded with 2–5 mm to the planning target volume (PTV) to account for organ motion and setup error. Margins depend on the site irradiated, with 2 mm margins for bony lesions and 5 mm for other sites. The type of organ at risk delineated depends on the localization of the metastasis. A planning organ at risk volume (PRV) expansion of 2 mm will be added for organs at risk (OAR) and dose constraints apply to this PRV. It is strongly recommended that dose constraints not be exceeded. If a dose constraint cannot be achieved due to overlap of the target with an organ at risk or its PRV, the fractionation can be increased or the target coverage compromised in order to meet the constraint. Treatment will be prescribed to the periphery of the target (80% of the dose) covering the 90% of the PTV. Dose constraints of organs at risk will be in accordance with the recommendations of the American Association of Physicist in Medicine (AAPM) task group 101 report [26].

#### Pembrolizumab

Pembrolizumab will be administered intravenously at a fixed dose of 200 mg per cycle. Pembrolizumab will be continued for up to 2 years until clinical progression or unacceptable toxicity. Pembrolizumab will be continued in clinically stable patients with initial evidence of disease progression. For suspected immune-related adverse reactions, adequate evaluation to confirm etiology or exclude other causes should be ensured. Based on the severity of the adverse reaction, pembrolizumab should be withheld and corticosteroids administered. Upon improvement to grade ≤1, corticosteroid taper should be initiated and continued over at least 1 month. Pembrolizumab may be restarted within 12 weeks after last dose of pembrolizumab if the adverse reaction remains at grade ≤1 and corticosteroid dose has been reduced to ≤10 mg prednisone or equivalent per day. Pembrolizumab must be permanently discontinued for any grade 3 immune related adverse reaction that recurs and for any grade 4 immune related adverse reaction toxicity, except for endocrinopathies that are controlled with replacement hormones. The subject may also discontinue protocol in case of intercurrent illness which would in the judgment of the investigator affect patient safety, the ability to deliver treatment or by request of the patient.

Subjects who stop pembrolizumab with stable disease or better may be eligible for up to 1 year of additional pembrolizumab therapy if they progress after stopping study treatment (only if the study remains open and the subject meets certain criteria).

#### Concomitant care

In general, medications or vaccinations specifically prohibited in the exclusion criteria are not allowed during the ongoing trial. Systemic glucocorticoids may be administered to modulate symptoms from an event of suspected immunologic etiology. All treatments that the investigator considers necessary for a subject’s welfare may be administered at the discretion of the investigator in keeping with the community standards of medical care. Adverse events will be managed according to most recent available guidelines.

### Follow-up

Patients will be seen before the start of each treatment cycle during the whole course of pembrolizumab therapy. At each visit, a history, directed physical examination and a routine laboratory blood analysis will be conducted with recording of the toxicity. Tumors will be re-evaluated every 9 weeks. A safety follow-up visit will find place approximately 30 days after the last dose of trial treatment or before the initiation of a new anti-cancer treatment, whichever comes first. Once a subject experiences confirmed disease progression or starts a new anti-cancer therapy, the subject moves into the survival follow-up phase and should be contacted by telephone every 12 weeks to assess for survival status until death, withdrawal of consent, or the end of the study, whichever occurs first. Subjects who discontinue trial treatment for a reason other than disease progression will move into the follow-up phase and will be assessed every 12 weeks by radiologic imaging to monitor disease status.

### Sample size

In the first phase of the trial 20 patients will be recruited and randomly assigned to a treatment arm. If the chance that the posterior toxicity probability rate exceeds 0.2 is more than 0.7 in a certain arm, this arm will be closed.

The secondary endpoint is the assessment of the response rate of the combination treatment in non-irradiated metastases in every arm. For this analysis a Simon’s two-stage optimum design will be used [29]. The arm with the best response rate and with acceptable toxicity will be used to proceed into the second phase. The null hypothesis that the true response rate is 0.21 [10] will be tested against a one-sided alternative. If there are two or fewer responses, the alternative hypothesis will be rejected. Otherwise 13 additional patients will be accrued for a phase II trial. The null hypothesis will be rejected if 7 or more responses are observed in 23 patients. This design yields a type I error rate of 0.15 and power of 0.8 when the true response rate is 0.41 (Table 2). We consider the chance that both arms in phase 1 are deemed safe with equal toxicity and equal response rates very small. Since both arms will then qualify to continue to phase 2, selection of one arm will depend on secondary outcomes available at that time (e.g. PFS, OS).

**Table 2 Tab2:** Simon’s two-stage optimum design

Optimal two stage design	Optimum design
First stage sample size (n1)	10
r1	2
Maximum sample size (n)	23
r2	6

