### Data analysis

The current trial aims to evaluate the safety of the combination treatment of pembrolizumab with SBRT and determine whether the sequence of these therapies matters. The primary endpoint is DLT assessed using CTCAE version 4.0. The SBRT schedule associated with DLT in <20% of patients will be determined based on the incidence of treatment-related adverse events.Response rates will be determined using RECIST v1.1. The null hypothesis that the true response rate is 0.21 [10] will be tested against a one-sided alternative. The null hypothesis will be rejected if seven or more responses are observed in 23 patients.Survival times are defined from the day of randomization until progression, last follow-up or death. Cases will be censored at last follow up visit if no progression was observed. Multivariate analysis will be performed according to the cox-regression method.For the evaluation of immunological markers, median values between two groups will be compared by the Mann–Whitney U test, between >2 groups with Kruskal–Wallis testing. To compare proportions of categorical variables, the Pearson’s Chi^2^ test or Fisher’s Exact test will be used. To evaluate correlations, Spearman correlation coefficients will be calculated. All statistical analyses will be performed using SPSS 24.0 (SPSS Inc, Chicago, IL, USA), a *P* value <0.05 will be considered statistically significant.When missing data occurs, analysis will find place with the available data. Due to the small sample size, no imputing will find place.

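### The stated type I error of 0.15 is for one pre-chosen arm; carrying the better of two arms into the same test makes it about 0.25 if both arms stay open

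*Protocol article*

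**What the plan says.** All of this is in the Sample size section of the protocol article and its Table 2.

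- Phase I randomises 20 patients to two arms, which differ in whether SBRT precedes the first or the third pembrolizumab cycle. An arm closes if its posterior toxicity crosses a stated limit.
- Selection: "The arm with the best response rate and with acceptable toxicity will be used to proceed into the second phase". The abstract describes the same selection. A tie is resolved on secondary outcomes.
- Hypothesis: "The null hypothesis that the true response rate is 0.21" and it "will be tested against a one-sided alternative".
- First stage: "If there are two or fewer responses, the alternative hypothesis will be rejected". "Otherwise 13 additional patients will be accrued for a phase II trial".
- Final rule: "The null hypothesis will be rejected if 7 or more responses are observed in 23 patients". The Data analysis section repeats it: "The null hypothesis will be rejected if seven or more responses are observed in 23 patients".
- Operating characteristics: "This design yields a type I error rate of 0.15 and power of 0.8 when the true response rate is 0.41".

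Table 2 gives n1 = 10, r1 = 2, n = 23, r2 = 6. Since 10 + 13 = 23, the selected arm's phase I patients form the first stage of the final test. No allowance for having chosen the better arm is stated in the abstract, Sample size, Table 2 or Data analysis.

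**The concern.** Simon's design assumes one arm, fixed before any response is seen. Here two arms compete on their stage 1 responses, the one with more goes forward, and those same responses are counted again in the test. The larger of two chance results exceeds a single chance result on average, so the first 10 patients in the final count start with a head start that the quoted error rate ignores.

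At stake is the trial's formal efficacy claim, that the combination does better than 0.21. A reader who takes the quoted 0.15 at face value expects a useless combination to be declared active about one time in seven. With both arms open it would be about one time in four. The quoted power also leaves open whether it covers choosing the right sequence, which is part of what the trial sets out to learn.

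**Working it through.** **Inputs** (Sample size and Table 2): p0 = 0.21, p1 = 0.41, n1 = 10, continue at 3 or more responses, n2 = 13, reject at 7 or more of 23. Ten patients per arm is taken from 20 patients in two arms together with n1 = 10.

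**Step 1: reproduce the stated figures for one fixed arm.**

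P(reject) = Σ over x = 3,…,10 of P(X1 = x) · P(X2 ≥ 7 − x), with X1 ~ Bin(10, p) and X2 ~ Bin(13, p).

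At p = 0.21 this gives 0.1466; at p = 0.41 it gives 0.8024. Both round to the stated values. A grid search over total sizes 10 to 35 also confirms that 10/2/23/6 is the optimum design for these targets. Table 2 is right.

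**Step 2: replace the fixed arm by the better of two.**

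Let M be the larger of two independent Bin(10, p) counts, so P(M = x) = F(x)² − F(x − 1)², where F is the binomial distribution function. The 13 new patients are unaffected. If both arms have the same true rate, a tie does not matter, provided the tie-break is unrelated to response, because both arms then bring the same count.

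Both arms at 0.21:

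| x | P(X1 = x), one arm | P(M = x), better of two | P(X2 ≥ 7 − x) | product, one arm | product, better of two |
|---|---|---|---|---|---|
| 3 | 0.2134 | 0.3219 | 0.2839 | 0.0606 | 0.0914 |
| 4 | 0.0993 | 0.1808 | 0.5347 | 0.0531 | 0.0967 |
| 5 | 0.0317 | 0.0618 | 0.7920 | 0.0251 | 0.0490 |
| 6 | 0.0070 | 0.0140 | 0.9533 | 0.0067 | 0.0133 |
| 7 or more | 0.0012 | 0.0023 | 1.0000 | 0.0012 | 0.0023 |
| Sum (unrounded terms) | 0.3526 | 0.5808 | | **0.1466** | **0.2527** |

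The chance of continuing rises from 0.353 to 0.581 and the chance of a false rejection from 0.147 to 0.253. A simulation of 2 million trials gave 0.253. Unequal splits of 9:11 and 8:12 give 0.257 and 0.252.

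**Step 3: allow for toxicity closure.** The protocol gives no closure probability. Assume each arm closes with probability q, independently of the other arm and of response, and that no test is made if both close. Then P(false rejection) = (1 − q)² · 0.2527 + 2q(1 − q) · 0.1466. For q = 0.10 this is 0.81 · 0.2527 + 0.18 · 0.1466 = 0.231.

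| q (assumed) | 0 | 0.05 | 0.10 | 0.20 | 0.30 |
|---|---|---|---|---|---|
| P(false rejection) | 0.253 | 0.242 | 0.231 | 0.209 | 0.185 |

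If exactly one arm is certain to remain, there is no selection and the figure is 0.147.

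**Step 4: power under selection** (all pairs of stage 1 counts enumerated, ties split evenly, neither arm closed).

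| True rates | Event | Reject at 7 or more | Reject at 8 or more |
|---|---|---|---|
| 0.21 and 0.21 | any rejection | 0.253 | 0.135 |
| 0.41 and 0.21 | good arm picked and H0 rejected | 0.733 | 0.673 |
| 0.41 and 0.21 | ineffective arm picked and H0 rejected | 0.066 | 0.038 |
| 0.41 and 0.21 | either of the two | 0.799 | 0.711 |
| 0.41 and 0.41 | any rejection | 0.946 | 0.889 |

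**Step 5: estimation.** With both arms at 0.21, the selected arm's stage 1 rate averages E(M)/10 = 0.281. Among trials that continue, the pooled 23-patient rate averages 0.276, but a single unselected arm that continues already averages 0.272.

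**The case against.** Four counter-arguments deserve weight.

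*The quoted numbers are right.* They are, for a single arm. A reader might infer that Table 2 is miscalculated; it is not. The fault lies in attaching its figures to a procedure with a selection step.

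*Response is a secondary endpoint, and 0.15 is a deliberately lenient level in a small uncontrolled screen.* This stands as a limit on the consequences: the primary safety conclusion and the patient numbers are untouched. It does not justify the figure, because the protocol sets a formal null, a rejection rule and an error rate, and the rate does not belong to the rule.

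*Toxicity closure can remove the selection.* It can, so 0.25 must not be quoted without its condition. In the assumed scenarios up to a 30% closure chance per arm, the error still exceeds 0.15.

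*Power holds.* A reader might infer that the stated 0.8 fails whenever only one sequence works. The documents do not support that. They do not say that power means picking the right arm as well as rejecting, and the chance of rejecting for whichever arm goes forward is 0.7985. What can be said is that this splits into 0.73 for the good arm and 0.07 for the ineffective one.

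It is also tempting to cite the pooled average of 0.276 against 0.21 as proof of selection bias. It is not: nearly all of that gap is the ordinary effect of looking only at trials that pass stage 1, and selection adds about 0.003.

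**Conclusion.** The concern holds as a multiplicity point about the design. The stated type I error of 0.15 describes one pre-chosen arm. For the select-then-test procedure that the protocol describes, it is about 0.25, given true rates of 0.21 in both arms, about 10 patients per arm, both arms open, and a tie-break unrelated to response. It moves towards 0.147 as closure of one arm becomes more likely; how far cannot be said, because the closure probability is not given. The stated power of 0.8 matches rejection for either arm when one arm is at 0.41 (0.80), overstates correct selection with rejection (0.73), and understates the case of two effective arms (0.95).

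**What to change.** **Main change.** In the Sample size section and Table 2, state that 0.15 and 0.8 apply to a single pre-chosen arm, and add the figures for the full procedure: type I error about 0.25 when both arms remain open and about 0.15 when only one does; with one arm at 0.41 and the other at 0.21, 0.80 for any rejection, made up of 0.73 for the good arm and 0.07 for the ineffective one; 0.95 with both at 0.41. This changes wording only.

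**If the sponsor wants the error at or below 0.15.** When both arms are candidates, reject at 8 or more of 23 (r2 = 7), and carry this into the Data analysis section. The error becomes 0.135 with no extra patients. The price is power: 0.67 for picking the good arm and rejecting when one arm is at 0.41 (0.71 for any rejection), and 0.89 when both are. Which error to favour is the sponsor's choice. Either change should be fixed before the responses that it governs are known.

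**Reporting.** Give the response rate in the 13 stage 2 patients beside the pooled 23-patient rate, because the selected arm's stage 1 rate averages 0.28 when the truth is 0.21. This costs nothing beyond one extra line in the results, although the estimate from 13 patients will be imprecise.
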